##### Annual prize draws

We will conduct an annual draw for which eligibility is based on 90% adherence over the course of the year. The aim is to encourage a sustained change in health behavior. The study coordinator will check the participant’s record and determine if the client is eligible for each annual draw. We will create a separate file for each client so that this check is easily performed.

#### Control group: usual care

The control group will receive care as usual, including any adherence support mechanisms within usual care practices. All clients receive intensive ART orientations and adherence education when they first start ART, but there is no systematic adherence support mechanism for long-term ART clients. However, adherence counseling is available to patients who are referred to a counselor by their providers. All control group participants are encouraged to come to the study offices at each clinic visit to ensure that they spend an equal amount of time with the study coordinator as those in the intervention groups. During that visit, we check the MEMS device and ask the client if they have any difficulties in using it.

### MEMS-cap procedures

Medications will be distributed in pill bottles with MEMS caps to patients in all three groups (including the control group) at recruitment (i.e., prior to random assignment) to avoid spurious intervention effects due to the MEMS cap. These caps house a microelectronic chip that records the date and time of each bottle opening, enabling a precise and objective assessment of the timing of each dose and the patient’s pattern of pill-taking. The study coordinator will assist the patient in dispensing a supply of the medication into a bottle we provide with an attached cap, or they can simply put the MEMS cap onto the actual medication bottle if preferred by the patient. We will monitor adherence to only one antiretroviral medication as studies show that rates of adherence do not differ significantly across medications taken by an individual patient [46]. Participants will be asked to use the cap continuously throughout the study and return with the bottle and cap for each clinic visit. We will ask patients to notify the study coordinator if their provider changes their regimen during the study so that the data can be downloaded and the medication being monitored can be switched with the new one. Participants will be informed that the cap records when the bottle is opened. They will also be informed that these data will not be shared with clinicians. We will carefully discuss the restrictions associated with the electronic cap with the patient. Solutions to potential concerns that are acceptable to both the patient and the project will be provided. Once a participant has started using the cap, we will review the instructions and restrictions with the participant at each clinic visit.

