### Inclusion criteria

Our study sample will be 330 HIV patients aged 18 and older who have been on ART at Mildmay for 2 years or longer to filter out clients who are at Mildmay only transiently and to target treatment-mature clients for whom it is likely that the motivational problems that are the target of our intervention are a significant barrier to adherence. They must have had recent adherence problems within the past 6 months based on clinical records (defined as showing lack of viral suppression, being sent to adherence counseling, or at disease stage 3 or 4 as per WHO guidelines). Our decision to enroll patients with adherence problems is based on our conceptual framework, which suggests that motivation is a key driver of adherence in treatment-mature HIV clients, as well as on meta-analysis data showing that HIV adherence interventions have a larger effect size for such clients (mean effect size 0.62) compared to effects on interventions applied to all patients (mean effect size 0.19), in general [44].

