##### Prize draws at each scheduled clinic visit

When participants in this group learn about their treatment assignment, they will be informed that if at their next visit they have taken their medication on 90% or more of occasions when they should have taken it, they will be eligible for the lottery. They will also be informed that for the next 24 months, they will continue being eligible for the lottery if they continue to take their medication at or above this level.

Each time the client attends a scheduled clinic visit, the study coordinator will check the client’s MEMS cap. The study coordinator will fill out a short form to verify eligibility that among other things asks the client whether they sometimes pocket doses (i.e., whether they take out more than one dose for a given opening). In a previous study, this was a relatively common practice used by about 15% of the sample. For example, many clients working as boda-boda or moped taxi drivers indicated that they commonly took the morning pill at home from the pill bottle, but pocketed the evening dose and took it with them as they did not know whether they would be home in time to take the evening dose. To avoid unfairly punishing those clients who pocket doses (which would show up as missing doses in the MEMS software, reducing their measured adherence), we will base their eligibility on their adherence over the last 2 weeks and ask them specifically about which days they pocketed doses. This method was easily implemented in our previous studies and was performed within a reasonable time (under 5 minutes per client who indicated pocketing).

If the client is eligible (> 90% adherence), they are invited to participate in the prize draw as described for the T1 group above. Previously, we sometimes observed that there was a discrepancy between the MEMS data and the client’s evaluation of their adherence. Therefore, we will let them enter into one draw a year when they did not reach the adherence threshold (as a wild card) to avoid disappointing the participant and to avoid unfairly punishing clients for whom there may have been an error in the MEMS-cap data. However, it will be made clear to the client that this is a one-time exception.

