##### Percentage of prescribed medication taken

Our behavioral primary outcome will be electronically monitored adherence. MEMS data will be collected continuously during the 24 months of the intervention period as well as for 12 months after the intervention ends, allowing us to investigate daily adherence and its timing. We will create a variable that captures the proportion of prescribed pills that were actually taken (i.e. number of actual bottle openings divided by the prescribed bottle openings).

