Anything that looks like it could be an adverse event will be brought to the attention of the local and study PIs, since each case needs to be investigated. Any unexpected or serious adverse events that occur during the course of this investigation and follow-up period will be reported by telephone by the PI within the next business day to the study institutional review boards (IRBs) and the independent study monitor. The telephone report will be followed within 3 business days by a written report, which will contain: the subject’s ID, the title and date of the serious adverse event, and a narrative explanation (e.g., how the research staff was notified of the event, dates of consent, screening results for inclusion or exclusion, whether the participant participated in the intervention or was in the control group, dates and circumstances of the hospitalization or death, and the participant’s status at their last clinical or research contact). In consultation with the IRBs, the PI will address whether there is a need to redesign or amend the protocol, or to inform current and future subjects of a change in how risks are described (e.g., changes to the consent form or protocol).

Except for adverse events, we do not expect that the interventions will need to be discontinued for any reason. As per our IRB protocol, participants are free to withdraw from the study at their own discretion. Due to the low-risk nature of the intervention, there will be no interim analyses or stopping rules.

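### The only stated route for updating prescribed openings after a regimen change is the patient's own report, and only T2 has a prize tied to that count

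*Protocol article*

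**What the plan says.** All references are to the protocol article.

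- **MEMS-cap procedures.** One drug per participant is followed: "We will monitor adherence to only one antiretroviral medication". On changes of treatment the text says "We will ask patients to notify the study coordinator if their provider changes their regimen during the study", so that the cap data can be downloaded and the new drug monitored instead. No other route is named.
- **Primary outcomes, Percentage of prescribed medication taken.** The outcome is the "number of actual bottle openings divided by the prescribed bottle openings". The section does not say where the prescribed count comes from once the regimen has changed.
- **Treatment group 2.** Clients qualify for a visit draw "if at their next visit they have taken their medication on 90% or more of occasions when they should have taken it". For the annual draw, "eligibility is based on 90% adherence over the course of the year". The T2 eligibility form also "asks the client whether they sometimes pocket doses".
- **Treatment group 1 and Control group.** T1 draws depend on keeping scheduled visits and on viral suppression. Controls have no draws; their cap is checked and they are asked about problems using it.
- **Randomization.** Staff who read the caps know the treatment arm.

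**The concern.** The denominator is a prescription, and a provider can change a prescription without the patient's behaviour changing. If the patient does not mention the change, two things can go wrong. A cap left on a stopped drug records missed doses that were never due. A reduction from two doses a day to one looks like a steady run of missed evening doses. The T2 section describes clients with morning and evening doses in an earlier study, so a change of frequency is a realistic case.

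Regimen changes are foreseeable. Entry requires a recent adherence problem, "defined as showing lack of viral suppression, being sent to adherence counseling, or at disease stage 3 or 4", only third-line patients are excluded on regimen grounds, and caps stay in use for 24 months plus 12.

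The incentive to report is unequal by design. A T2 client gains by reporting a switch or reduction that would otherwise look like missed doses, and gains by not reporting an increase. T1 and control clients have neither reason. T2 visits also include an eligibility form with questions about doses, and the reading is unblinded.

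The contrast most exposed is T2 versus T1, which the Discussion presents as the choice between rewarding measured adherence and rewarding suppression. The secondary outcome of taking at least 90% of pills is more fragile than the mean, because a short mis-scored spell can push one person across the threshold.

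**Working it through.** **Inputs from the article (Sample size and power).** Mean MEMS adherence about 75%. Stated detectable differences: 6.5 points (T1 and T2 combined versus control) and 7.5 points (T2 versus T1) at month 12; about 7 and 8 points at month 24. Power 80%, two-sided. Attrition 10% a year, so 110 × 0.9 = 99 per arm at month 12 and 99 × 0.9 = 89.1 at month 24. No SD and no significance level are given; I assume 0.05.

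**Step 1: the plan's own figures.** With no SD they cannot be computed forward, so I solve for the SD: SD = δ / [(1.960 + 0.842) × √(1/n + 1/(rn))], with r = 2 for the combined contrast and r = 1 for the pairwise one.

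- Month 12: 6.5 points gives 0.188; 7.5 points gives 0.188.
- Month 24: 7 points gives 0.193; 8 points gives 0.191.

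The four figures agree with one another at an SD near 0.19, so they are a fair yardstick for the bias.

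**Step 2: loss per unreported change, while it lasts.**

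- Twice daily to once daily, denominator not updated: 75 × 0.5 = 37.5 points.
- Cap left on a stopped drug, scored zero: 75 points.

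**Step 3: between-arm bias.** Bias = share switched × between-arm difference in reporting × share of period affected × loss. The first three are assumptions; the article gives none of them.

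| Switched | Reporting difference | Share of period | Frequency halved | Cap on stopped drug |
|---|---|---|---|---|
| 5% | 25% | 50% | 0.2 | 0.5 |
| 10% | 50% | 50% | 0.9 | 1.9 |
| 20% | 100% | 100% | 7.5 | 15.0 |

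Middle row: 0.10 × 0.50 × 0.50 × 37.5 = 0.94, and × 75 = 1.88. The last row is an outer bound, not a forecast.

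**Step 4: if the next visit catches the change.** Visits are 2 to 3 months apart. With 10% switched and a 50% reporting difference:

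- smallest case, 2 of 24 months, frequency halved: 0.10 × 0.50 × 2/24 × 37.5 = 0.16;
- largest case, 3 of 12 months, stopped drug: 0.10 × 0.50 × 3/12 × 75 = 0.94.

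So early detection brings the bias to roughly 0.2 to 0.9 points.

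**Step 5: what would match a 7.5-point detectable difference.** A net between-arm difference in unreported changes of 7.5/37.5 = 20% of participants, or 7.5/75 = 10%, lasting the whole period.

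**Step 6: the 90% threshold.** Three months scored zero limits a fully adherent person to 21/24 = 87.5% over 24 months. Two months limits them to 10/12 = 83.3% over a year, which fails the annual T2 draw.

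**The case against.** The best defence is that this is a condensed article. Rules for deriving the denominator usually sit in the full protocol or SAP, and coordinators already see bottle and cap at visits and can use clinic records. That is right about derivation detail, and it means patient report can only be called the only *stated* route. It does not dispose of the point, because the article does state a procedure for regimen changes, and that procedure relies on the patient.

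Several limits stand:

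- A switch at the same dosing frequency with the cap moved to the new bottle is scored correctly. A change to an unmonitored drug has no effect.
- Entry through adherence counselling is enough, and randomization is stratified by detectable or undetectable viral load, so not every participant is a likely switcher.
- The motive is modest. A visit draw is worth 0.25 × (0.50 + 1.00 + 1.50) = USD 0.75 on average. Differential reporting is plausible, not shown.
- The direction is open: T2 clients might report sooner, or might conceal a change. Limitations already concedes that openings may be manipulated for prizes.
- In the combined contrast, if T1 reports like control, the bias is half that for T2 alone.

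A reader might infer three stronger things. One is a change unreported for 12 months, which would cost that person 75 × 12/24 = 37.5 points; with cap checks every 2 to 3 months, so long a delay is unlikely. Another is that hospital stays are wrongly scored: the article mentions "dates and circumstances of the hospitalization or death" only as an example item in an adverse event report, and its silence about MEMS handling may be condensation. At an assumed 5% admitted for 10 days, the arm mean moves only 0.05 × 10/365 × 75 = 0.1 point. The third is a safety problem from rewarding openings of a stopped drug, which is speculative because an opening is not ingestion.

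**Conclusion.** The point holds in limited form. The stated procedure lets an unreported change to the monitored drug or its dosing frequency count as adherence behaviour, and only T2 has a prize linked to reporting it. Under moderate assumptions (10% switched, 50% reporting difference, half the period affected, 75% true adherence) the bias is about 1 to 2 points, and under 1 point if the next visit catches the change. This is below the stated 6.5 to 8 points and would not by itself manufacture an effect of that size.

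It is still worth preventing. The regression models adjust for arm, period and baseline covariates, and the attrition weights address dropout; none of these recognises a wrong denominator. More follow-up would not average out an error that differs by arm. All sizes rest on assumed switching and reporting rates, and the sign is not known.

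**What to change.** In MEMS-cap procedures, have the coordinator check the current regimen and dosing frequency in the clinic record at each existing visit, in the same way in all three arms, with patient notification kept as a supplement. Date any change from the record and move the cap to the newly prescribed medication.

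In the definition of the behavioural primary outcome, state that prescribed openings follow the recorded regimen and are updated from the recorded date of change. Use the same count for T2 visit and annual eligibility.

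The check has to be made during follow-up, so that caps are moved on time. Records are already used for T1 appointments, viral loads and part of the baseline medical history, so the cost is a few minutes of coordinator time per visit and one derivation rule.

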### Study timeline

#### Recruitment

During recruitment (also called the pre-baseline visit), the client will be given a MEMS cap, which will be used to track baseline adherence and study eligibility for 2–3 months (depending on the date of the client’s next scheduled clinic visit). During the recruitment phase, clients will be consented to participate by study coordinators, and for some (about 120 in total), we will administer short, 30-min qualitative interviews (Section 2.13.2). Participants will be compensated with 20,000 USh for their time. They will be paid for completing questionnaires even if this does not happen on a scheduled clinic visit, such as when they come in late or early for a clinic appointment.

As appointment dates are readily available from the electronic medical records system, we can print out weekly lists of eligible clients together with when they are expected at the clinic and when they are scheduled for their next viral load test. We will enroll clients on the day of or within 3 months of their annual viral load test to synchronize the viral load testing with the study timeline. Doing so will allow us to benefit from existing clinic procedures and reduce the inconvenience and transport costs of the intervention for clients. Thus, participants will not take any additional viral load tests or attend additional clinic visits for the study. We will provide this list of participants to the study coordinator, who can then watch out for these clients in collaboration with the clinic receptionist.

We will consent and enroll 4–6 clients per day (some clients may refuse participation, though this has been rare in our previous studies) during the 6- to 9-month recruitment period. Based on the large clinic population and our previous experience, we expect to recruit 330 clients easily within a 6-month period but we have allowed sufficient extra time to accommodate for the clinic being closed on public holidays and for any other delays.

#### Baseline survey and randomization

When a client returns for their next scheduled clinic visit after recruitment (after about 2–3 months), we will conduct the baseline survey, reveal their treatment assignment to either the control or one of the two intervention groups, and begin the intervention. We will exclude all clients who did not open the MEMS cap for at least 30% of the days during the pre-baseline period as consistent use of the MEMS cap is essential for participation in the study. This second visit will (just as the first one) coincide with a scheduled clinic visit so that participants do not have to come to the clinic solely to participate in study activities.

The baseline survey contains information about:
demographics and socioeconomic status, including age, gender, education, relationship status, employment type and status, income, housing, economic shocks, and household compositionmedical history, including history of opportunistic infections, health-seeking behavior, current medications and length of time on current drug regimen, and WHO HIV disease stage, some of which will be taken from their medical recordsphysical symptoms and side effects, for example, respondents will be asked how “bothersome” and “disruptive” (in separate items) any symptoms perceived to have been caused by their medication in the past month have beenreasons for non-adherence or failure to seek care; we will use an 11-item module regarding reasons for non-adherence developed by the AIDS Clinical Trials Group that we slightly modified to fit the Ugandan context that asks participants to indicate whether listed items were reasons for not taking their medication in the previous month or seeking care, such as “when the drugs make you feel bad,” or “when your daily routine is interrupted,” or “lacked resources”

We use the Intrinsic Motivation Inventory to examine participants’ subjective experiences of taking medications [47]. The survey will also collect information on behavioral economics biases, such as present bias or risk preferences.

#### Follow-up surveys

Follow-up surveys will be conducted at months 6, 12, 18, and 24. These assessments will allow us to collect several data points for each participant on mediators or moderators that we believe may be influenced by the intervention (e.g., cognitive and motivational factors). After the intervention is finished, we will continue to track the adherence of participants for 12 months to assess whether the intervention encourages adherence persistence after incentives are withdrawn.

#### Exit interviews

Altogether, 40 participants will be asked to attend a semi-structured exit interview after they have completed the 24-month intervention period. We will stratify the sample by gender and recruit people from each of the three study arms. The interview will address topics such as barriers and challenges related to ART adherence and attending scheduled clinic visits. Intervention participants will also be asked about barriers and challenges they may have faced during the intervention, and we will elicit feedback on their experience in the BEST program.

This semi-structured interview will be conducted by the study coordinator at Mildmay clinic on the day of a scheduled visit and will last approximately 30 min. Interviews will be audio recorded with the permission of the participant, and then translated and transcribed. The audio recording will be deleted once the transcription is complete. Hardcopy notes will be digitized and transferred to RAND via secure online transfer. Hardcopy notes will be stored at Mildmay and accessible only to study staff.

### Outcomes

#### Primary outcomes

We have one biological primary outcome and one behavioral primary outcome.

##### Viral suppression

Our biological primary outcome will be a binary indicator for whether the participant has an undetectable viral load. The AIDS Clinical Trials Group defines virologic failure as a confirmed viral load > 200 copies/mL. We will consider that a viral load is undetectable if it is below 200 copies/mL. Viral load is the primary measure used to assess the level of viral activity in a person’s blood, as well as their response to ART. Although other factors besides adherence contribute to viral load, having an undetectable viral load is widely considered a strong indicator of good ART adherence. Furthermore, given the limitations of measures of behavioral adherence, viral load is considered by some to be the best indicator of adherence, and at the very least a valuable complement to behavioral adherence measures. Viral load measurements are now– part of routine clinical care at Mildmay and results for participants will be taken from clinical records. Viral load is measured when a person receives a positive HIV test result, after 6 and 12 months, and then every 12 months. We will synchronize recruitment so that the viral load of all participants is assessed at baseline, around month 12, and around month 24.

